## Abstract

**Background and aims::**

There are conflicting data regarding the use of propofol in the intensive care unit. The present study aims to explore the propofol dose-response relationship in the context of associations with clinical outcomes. Here we present the data collection and analysis procedures.

**Methods and analysis::**

The International Nutrition Survey (www.criticalcarenutrition.com) contains data from 785 medical, surgical, or trauma intensive care units. This survey also includes data on daily mechanical ventilation and propofol use, along with the associated propofol-related energy intake. Of the 21,100 adult patients, we will analyze those who spent at least 48 hours in the intensive care unit. Data collection will include patient characteristics, propofol parameters, use of mechanical ventilation, severity of illness at intensive care unit admission, and time to discharge alive or in-hospital death. In addition to the duration of propofol therapy (days), propofol-associated fat intake will be used as a surrogate for propofol dose. Statistical analyses will use multistate models and piece-wise exponential additive mixed models to examine associations between propofol use (including associated fat intake) and outcomes, while adjusting for numerous confounders and accounting for mechanical ventilation.

**Ethics and dissemination::**

Institutional ethics approval was granted by the Health Sciences Research Ethics Board at Queen's University, Kingston, Ontario (file number 6004791). Informed patient consent was not required due to the nature of this study. Procedures were conducted in accordance with the ethical standards of the institutional or regional committee for human experimentation and the Helsinki Declaration of 1975.

## INTRODUCTION

Recently, controversy has arisen regarding whether propofol has undesirable side effects compared to other sedative drugs.^(1)^ These effects may mainly occur in patients over 65 years of age,^(2)^ but have also been observed in pediatric populations.^(3)^ A meta-analysis by Kotani et al.^(1)^ involving 252 randomized controlled trials and more than 30,000 patients found that the use of propofol is associated with a potential 10% increase in mortality compared with other sedation strategies. This fatal side effect may also be relevant for critically ill patients, for whom there was a 10% relative increase in mortality (15% *versus* 13%), with a Bayesian approach indicating a 75.7% probability of harm.^(4)^

In contrast, other meta-analyses have found that, compared to midazolam, the use of propofol does not worsen the outcome for a heterogeneous population of critically ill adult patients,^(5)^ and may even reduce the length of stay in the intensive care unit (ICU), the duration of mechanical ventilation (MV) and the time to extubation for acutely ill surgical patients.^(6)^ Two recent meta-analyses compared propofol with dexmedetomidine. On the one hand, there was no difference in mortality.^(7,8)^ However, in the meta-analysis by Heybati et al.,^(7)^ for example, mortality was only an endpoint in four trials involving 364 patients. This small sample size may have contributed to the very low certainty of these negative results. Conversely, Heybati et al.^(7)^ found that propofol may increase the duration of MV and lengthen hospital stays for unselected patients, as well as increasing the risk of ICU-associated *delirium* in cardiac surgery patients.

So far, no study has examined the dose-dependent effects of propofol on outcomes in scenarios where the maximum application rate of 4 - 5mg/kg per hour or 95 - 120mg/kg per day has not been exceeded. Furthermore, examinations of the effects of prolonged propofol administration in controlled studies have been limited to a maximum of five days.^(7)^ It is currently unknown whether the critical illness phase (early or late) in which propofol is administered also affects its unwanted effects. There is also little information on the effect of cumulative propofol doses on outcomes. A recent monocentric retrospective observational study of 839 critically ill, mechanically ventilated patients found no association between substantial cumulative propofol doses (> 500mg) and 6-month mortality.^(9)^ However, it should be noted that, without adjustment for confounders, a high cumulative dose of propofol was associated with shorter survival. This association only disappeared after adjustment, which may be related to the relatively small number of patients studied (less than 1,000).

The primary purpose of this study is to investigate the relationship between the duration of propofol therapy and daily/cumulative propofol-associated energy intake and outcomes.

### Research question

The average causal effect of propofol on the risk of in-hospital all-cause death has been demonstrated in previous clinical trials. Associations between propofol doses, timing, and responses, however, are unknown. The present study aims to fill this gap. The primary research question focuses on the association between defined levels of propofol-associated energy intake in the early and late phases following ICU admission and competing risks (time to discharge alive (being a surrogate of morbidity), and in-hospital death, respectively). The secondary research question centers on the association between preceding cumulated or daily propofol energy intake, or the number of days on propofol prior to transitioning from propofol to, e.g., death or being free of propofol the day after transitioning. These factors will be examined in terms of measured variables and transition probabilities, while accounting for bias from confounding by indication or palliative care. The general aim is to provide more evidence on safe propofol dosing and duration.

## METHODS

### Data base

The International Nutrition Survey is a multinational database of critically ill adults treated in 785 international medical, surgical, or trauma ICUs. This database includes, in addition to nutritional and outcome data, information on daily propofol use and associated fatty acid intake and has collected data on more than 20,000 critically ill patients. Details of this database have been presented in a previous publication, and to date, the results of 18 previous studies have been based on various subgroups included in this database. Details of these studies, which addressed various aspects related to medical nutrition therapy, can be found in the electronic database.^(9)^

The core of the present study will be the analysis of a subpopulation of this multinational database. Patients enrolled in this database were followed from the day of ICU admission. Nutritional and clinical parameters (including daily protein intake, lipid intake, use of MV, propofol, and propofol-associated fat energy intake (including soybean oil and purified egg phosphatide) were collected daily from Day 0 (day of ICU admission) until ICU discharge or death, or for a maximum of 12 days for patients still in the ICU. Survival was assessed until hospital discharge (dead or alive) up to 60 days from ICU admission. Only ICUs with at least one included patient were kept in the database.

During the ICU stay, patients received standard medical care (including MV and propofol) at the treating physician's clinical judgement. The principles of sedation, ventilation strategies, including lung protective ventilation, weaning, and prevention/therapy of ventilator-associated pneumonia, followed international guidelines in effect at the time of the data collection.^(10-13)^

### Selection of the study population

#### Inclusion criteria

Patients selected from the database will be aged 18 years or over and have a body mass index (BMI) of over 13kg/m^2^. Other inclusion criteria will be an ICU length-of-stay (LOS) of > 48 hours. The rationale behind this inclusion criterion is that the potentially detrimental effects of propofol on survival are not attributable to immediate or acute reactions, but instead require more than 48 hours of therapy to manifest (e.g., in the event of propofol infusion syndrome).^(1,14)^

For patients admitted to the same unit during the same hospital stay, we will only analyze the first ICU admission. Patients readmitted after hospital discharge will be included as separate cases.

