### Statistical analysis plan

#### Descriptive analysis

Continuous variables are described by mean, SD, median, minimum, and maximum values. In addition, two-sided 95%CIs are calculated for continuous variables. Additional descriptive statistics may be calculated as needed (e.g., quartiles, coefficient of variation, etc.). In particular, the median and interquartile range (IQR) are used to describe non-normally distributed data. Frequencies and corresponding percentages per class level describe categorical variables. Patients with missing data will be excluded. However, we will examine where and how frequently missing values occur in the data overall, how often they co-occur across variables, and whether there are notable patterns of missingness across groups. We will then derive possible limitations of this study from that analysis.

For the competing risk analyses (time-to-discharge alive, time to in-hospital death), we will classify daily propofol-associated energy intake using three thresholds that define three different levels based on the amount of propofol-associated energy received. The identification of specific energy thresholds will be based on clinical practice:^(18,19)^ level I: < 1.0kcal propofol-associated energy/kg per day; level II: 1.5 - 4.5kcal propofol-associated energy/kg per day; level III: > 4.5kcal propofol-associated energy/kg per day). Suppose there is a highly uneven distribution of patient days with a given level of propofol-associated energy intake. In that case, energy thresholds may be redefined after preliminary exploratory analysis of these data, but before assessing the association with outcome.

For converting propofol-associated energy intake into mg propofol, we will assume that the use of 1% and 2% propofol in the present study was similar to that in the multinational EuroPN study on medical nutrition therapy (2% propofol: 62%, 1% propofol: 37%, unknown: 1%; unpublished observations of the EuroPN study).^(20)^ From these data, it is possible to convert propofol-associated energy intake into mg propofol. According to Appendix A, the energy levels above would roughly correspond to the following propofol dose levels: level I: < 20mg/kg per day; level II: 20 - 60mg/kg per day; level III: > 60mg/kg per day. These propofol categories, however, will only be used to interpret results. For all statistical analyses, we will use the levels defined above based on propofol-associated energy intake.

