### Subgroup analysis

In order to look at associations according to admission diagnosis, sex and age, the results will be analyzed separately for female patients, surgical patients with a cardio-vascular admission diagnosis, patients who only had a low propofol-associated energy intake during the first 48 hours after ICU admission (daily propofol-associated energy intake (level I): < 1.5kcal/kg per day), patients younger than 65 years and patients with an admission APACHE II score ≥ 25.

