### Sensitivity analysis for the competing risk models used to analyze time-to-discharge alive/in-hospital death

When analyzing the cumulative association between propofol-associated energy intake and these outcomes, we will use a lag time of two days to minimize indication bias due to lower doses approaching discharge (or to higher doses before death). Consequently, the time window (defined by the lead time, see above) for which cumulated associations of propofol-associated energy intake with time-to-discharge alive/in-hospital death are calculated will be shortened by two days.

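### The low-intake reference level has no lower bound, so ICU days without propofol are pooled with low-dose days in the primary intermediate-versus-low contrasts

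*Protocol article*

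**What the plan says.** The protocol article (Abstract) states the aim as follows: "The present study aims to explore the propofol dose-response relationship in the context of associations with clinical outcomes". Propofol is not a condition of entry. Inclusion criteria asks for a minimum ICU stay ("Other inclusion criteria will be an ICU length-of-stay (LOS) of > 48 hours"), and Data base records that "patients received standard medical care (including MV and propofol) at the treating physician's clinical judgement".

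For the competing-risk analyses, Descriptive analysis defines three levels of daily propofol-associated energy intake, the lowest being "level I: < 1.0kcal propofol-associated energy/kg per day". Subgroup analysis gives the same level another bound: "daily propofol-associated energy intake (level I): < 1.5kcal/kg per day". Neither version has a lower limit, and no level is reserved for zero intake.

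The section on the overall design of the competing risk models assigns an intake value to each day after ICU admission and fills in 0 after ICU discharge. It plans six pairwise comparisons: intermediate versus low and high versus intermediate, each for the early phase, the late phase and both together. Outcome measures sets the lead time at twice a patient's number of propofol days and counts events from day 2.

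**The concern.** A dose-response contrast should compare two doses. If the lower category also holds ICU days without any propofol, the comparison mixes two questions: more propofol against less, and propofol against none. The second is tied closely to the need for sedation. A patient whose propofol has been stopped is usually at a different point in the illness from one on a small running dose.

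The protocol recognises this elsewhere. Its sensitivity analysis for the multistate models treats the move from propofol to no propofol as a marker of recovery unless palliative care explains it, and the multistate model keeps propofol and no propofol as separate states. The primary categorised analysis drops that distinction. At stake is whether the three intermediate-versus-low hazard ratios can be read as effects of dose, which is what the study sets out to report.

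**Working it through.** **The plan's own figure.** Sample size considerations gives more than 18,000 patients and a discharge-alive rate of about 70%: 18,000 × 0.70 = 12,600, in line with the stated more than 10,000 discharges. That figure is sound and does not bear on the point, except that adding an exposure level leaves patients and events unchanged.

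**Where a zero day falls.** 0 < 1.0 and 0 < 1.5, so a 0 kcal day is level I under either printed bound.

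**Which contrasts use level I.** 3 phase definitions × 2 comparisons = 6. Three (intermediate versus low) have level I as reference. Three (high versus intermediate) compare the two upper levels and do not use it.

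**Whose zero days they are.** Lead time = 2 × propofol days.

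| Propofol days | Lead time (days) |
|---|---|
| 0 | 0 |
| 1 | 2 |
| 2 | 4 |
| 3 | 6 |
| 5 | 10 |

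Events count only from day 2, so a never-user, read literally, has no event window. The zeros that matter come mainly from recipients. If the window runs from ICU admission, as Outcome measures suggests, and contains all d propofol days, then 2d − d = d of its days are without propofol. With d = 3, that is 3 of 6 days. Some of these are ICU days and some may be zeros filled in after ICU discharge; the document does not give the split.

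**What adjustment covers.** In Table 1, the count of ventilation days on Days 0 to 2 is the ventilation covariate for the categorised analysis. The count running to Day 11 is reserved for the multistate models. For the late phase (Days 5 to 11), nothing in the competing-risk model reflects whether the patient is still ventilated, so stopping sedation and weaning can appear as an effect of lower intake.

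**How far the reference moves.** Assumption: low-dose days average 0.5 kcal/kg. With 25%, 50% or 75% zero days in level I, mean intake in the reference is 0.5 × 0.75 = 0.375, 0.5 × 0.50 = 0.25 or 0.5 × 0.25 = 0.125 kcal/kg per day. The true share is not given.

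**Direction.** Let z be the share of zero days in level I and r the event hazard on zero days divided by that on low-dose days. If dose had no effect, a simple day-level mixture gives an intermediate-versus-low hazard ratio of 1/(1 + z(r − 1)). This is below 1 when r > 1, above 1 when r < 1, and equal to 1 when r = 1. Recovery after stopping suggests r > 1 for discharge alive. A switch to other drugs at the end of life, which the protocol also describes, would raise the hazard of death on zero days.

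**The case against.** Several points on the other side stand.

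- **Entry criterion.** A reader might infer that the entry rule is wrong, because its rationale is that harms "require more than 48 hours of therapy to manifest" while the rule counts time in the ICU. The wording is loose, but a stay over 48 hours is necessary for more than 48 hours of therapy, and the multistate models need states without propofol. Requiring later propofol for entry would condition on future exposure and survival. Entry should stay as it is.
- **Lag.** A reader might also infer that the 48-hour premise rules out effects of recent doses, so that the lagged model should be primary. The premise concerns duration of therapy, not latency: a patient on the sixth propofol day already meets it. The plan also has a sensitivity analysis for this bias: "we will use a lag time of two days to minimize indication bias due to lower doses approaching discharge". Making it primary is a trade-off, since one propofol day would leave 2 − 2 = 0 days of window and two would leave 4 − 2 = 2.
- **Size.** Hazard ratios can be produced by choosing z and r, but neither is in the document. The mixture formula is also unadjusted and works on single days, whereas the plan fits an adjusted cumulative-exposure model for hospital outcomes. Such figures would not be evidence of magnitude.
- **Day counting.** The design section once numbers the phases by days on propofol, which could exclude zero days. Its opening sentence, its description of the exposure history and Exposure variables all count days after ICU admission.
- **Cover elsewhere.** The multistate models do separate propofol from no propofol, but they are secondary and address ICU transitions. The low-intake subgroup again mixes zero with low. Limitations says that all models adjust for ventilation duration, but Table 1 gives the competing-risk models the Days 0 to 2 count only. Thresholds may be redefined if patient-days are very unevenly spread, but nothing commits the plan to a zero level.

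**Conclusion.** The point holds for the three intermediate-versus-low contrasts of the primary categorised analysis. As written, their reference pools ICU days without propofol with low-dose days, and the available adjustment does not separate the two. These hazard ratios therefore cannot be read purely as comparisons of two doses. The high-versus-intermediate contrasts, the entry criterion and the place of the lagged model are not at fault on this point.

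The conclusion rests on two readings: that exposure is indexed by day after ICU admission, and that the lead-time rule is applied literally, so that the zeros belong mainly to recipients who have stopped. The size cannot be derived from the document. The direction depends on the hazard on zero days relative to low-dose days and may differ between discharge and death. This is a worthwhile and inexpensive improvement, not a defect that invalidates the design.

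**What to change.** Before any association with outcome is examined:

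1. Reconcile the two bounds for level I (1.0 and 1.5 kcal/kg per day) with the start of level II, which is printed as 1.5.
2. Split level I into no propofol (0 kcal) and low (above 0, up to the level II threshold).
3. Build the hypothetical low pattern from the low level, take intermediate versus low among propofol days only, and report no propofol as a separate category.
4. State how never-users, whose lead time is zero, enter the competing-risk model.
5. Say whether the low-intake subgroup includes patients with zero intake.

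The cost is one extra exposure level, a smaller reference category and wider confidence intervals for intermediate versus low. Patients and events stay at about 18,000 and 12,600, and the plan already allows thresholds to be revised at this stage. The split makes the contrast a comparison of doses. It does not remove confounding by indication, since a low dose may itself be a step towards stopping.

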#### Data collection

Using a secure web-based data collection tool, the following information was collected: date of ICU admission, admission category (elective surgery, emergency surgery, and medical), primary admission diagnosis (nine categories), sex, age, BMI, daily use of MV/propofol therapy, and Apache II score on the day of admission. Attending physicians or allied healthcare professionals with expertise in nutrition practices (e.g., dietitians) also recorded daily protein intake and route of additional caloric intake (enteral nutrition, parenteral nutrition). For the first 11 days after ICU admission, the database contains information on protein and energy intake, as well as the number of days on which a patient received parenteral nutrition or oral feeding at any time.

Daily propofol-associated energy intake was also collected from the day of ICU admission (partial day) to a maximum of 11 additional days after admission. Information on the exact dose of propofol (administered via 1% or 2% solutions) was not available in the database. However, as propofol-associated energy intake is closely related to the dose of propofol, propofol-associated energy intake can be used as a surrogate parameter for this dose (1mL of a solution containing propofol contains 50mg of soybean oil, and 50mg of purified egg phosphatide, equivalent to 1.1kcal/mL).

Patients were followed in the hospital for a maximum of 60 days after ICU admission. We recorded the time to in-hospital death or discharge alive. Patients who remained alive in the hospital for more than 60 days were considered censored for both risks at that time.

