### Confounder variables

The list of confounder variables is presented in table 1. To account for heterogeneity across ICUs, all models will include random effects for each unit.

**Table 1 t1:** List of confounder variables. In addition to these variables, all models will contain a random intensive care unit variable

Variable	Time of recording
Number of days on oral nutrition	Days 0 - 2 post ICU admission
Number of days on parenteral nutrition	Days 0 - 2 post ICU admission
Number of days with protein intake > 1.2g/kg day	Days 0 - 2 post ICU admission
Year of therapy	Admission date
APACHE II score	ICU admission
Main admission diagnosis*	ICU admission
Admission category (surgical elective/emergency, medical)	ICU admission
Age	ICU admission
Sex	ICU admission
BMI	Pre-ICU admission
Baseline number of days under MV†	Days 0 - 2 post ICU admission
Number of days under MV before state transition‡	Days 0 - 11 post ICU admission

ICU – intensive care unit; APACHE - Acute Physiology and Chronic Health Evaluation; BMI - body mass index; MV - mechanical ventilation.

* Gastrointestinal, cardio-vascular, metabolic, neurologic, orthopedic/ trauma, renal, pulmonary, sepsis, other. Sepsis was the main admission diagnosis, if there was an infection-associated circulatory dysfunction requiring vasopressor therapy which dominated dysfunction of other organs;

† only used when analyzing the association of daily propofol-associated energy intake (categorized variable) with time-to-discharge alive/in-hospital death (cumulated for the early and late phase after intensive care unit admission);

‡ only used in multistate models

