### Outcome measures

–**Primary outcomes:** time-to-hospital discharge-alive as a surrogate of morbidity, and to in-hospital death (adjusted hazard ratios and 95% confidence intervals [95%CI]).Adjusted hazard ratios compare two levels of daily propofol-associated energy intake. They will be calculated separately for each day after ICU admission using sub-distributional and cause-specific hazard models. The observation period will start on the day of ICU admission, and events (day of discharge alive/in-hospital death) will be registered from day 2 after ICU admission until the end of the lead-time (defined as twice the number of days that a patient received propofol therapy).–**Secondary outcomes:** the risk of state transition (adjusted hazard ratio and 95%CI) and the transition probabilities between the different states (Figure 1).State transition risks and probabilities will be referred to a certain amount of propofol-associated energy intake or a specific duration of propofol therapy; adjusted hazard ratios will be calculated for all 17 transitions (Figure 1). State transition will be registered until day 13 after ICU admission. Initial and absorbing states include "propofol: no/MV: no", "propofol: yes/MV: no", "propofol: no/MV: yes", "propofol: yes/MV: yes", post-transition absorbing states include "in-ICU death" and "ICU discharge alive.

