### Data management plan

All data collected during the study were recorded by designated site personnel in a dedicated repository and stored in a study-specific database.^(17)^ Data from this database were transferred to an electronic data management system that complies with the guidelines for Good Automated Manufacturing Practice, version 5.0 (GAMP 5; INES, IQVIA, Paris, France). All patient data are pseudonymized and coded with a unique patient identification (ID) number generated by the electronic data management system. The database complies with all applicable national, regional, and local regulations on patient data protection and record keeping. Data analysis will be performed using R statistical software. Details of the study will be reported in accordance with the Strengthening the Reporting of Observational Studies in Epidemiology (STROBE) guidelines.

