### Overall design of the competing risk models used to analyze time to discharge alive and to in-hospital death

The primary aim will be to analyze the association between daily propofol-associated energy intake from day 1 to day 11 after ICU admission and the time to the hospital endpoint (discharge alive with in-hospital death as a competing risk).

Recording of propofol-associated energy intake was stopped if a patient died, was discharged from the ICU, or was in the ICU for more than 11 days. However, our statistical model requires information on propofol-associated energy intake on propofol days 1 to 11 after ICU admission for all surviving patients, even if patients were discharged from the ICU before day 11. Assuming no propofol-associated energy intake after ICU discharge alive, we will impute a daily propofol-associated energy intake of 0 for these patients.

To account for the fact that a short duration of propofol therapy (and propofol-associated energy intake) may not affect outcome over a more extended period, we will use a lead-time defined as twice the number of days that a patient received propofol therapy. These lead times provide a window in which propofol-associated energy intake on a given day could have affected the subsequent day of discharge alive (time to discharge alive).

To facilitate the interpretation of the associations between propofol-associated energy intake and outcome estimated by our model, we will construct five different hypothetical propofol-associated energy intake use patterns (reflecting three different levels of daily propofol-associated energy intake (low, medium, high) on propofol days 1 to 11). These levels of use will also be used to model associations between propofol-associated energy intake and outcomes. Similar to our recent publications,^(9,15)^ we will distinguish between an early (days on propofol #0 to #4) and a late (days on propofol #5 to #11) acute phase.

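### Repeat ICU records of one patient are analysed as independent cases, and an ICU return within days 0–11 is coded as zero propofol intake; the effect on precision is probably small

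*Protocol article*

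**What the plan says.** All references are to the protocol article.

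- **Inclusion criteria**, within one hospital stay: "For patients admitted to the same unit during the same hospital stay, we will only analyze the first ICU admission". After hospital discharge: "Patients readmitted after hospital discharge will be included as separate cases". No rule is given for a second admission to a different participating unit during the same hospital stay.
- **Confounder variables**: "To account for heterogeneity across ICUs, all models will include random effects for each unit". The caption of Table 1 repeats this: "In addition to these variables, all models will contain a random intensive care unit variable". No patient-level term is named.
- **Outcome measures**: the primary outcomes are "time-to-hospital discharge-alive as a surrogate of morbidity, and to in-hospital death", both events of the hospital stay. They are registered from day 2 until the end of a lead-time equal to twice the patient's number of propofol days.
- **Data collection**: "Patients were followed in the hospital for a maximum of 60 days after ICU admission". The clock of each record therefore starts at its own ICU admission.
- **Overall design of the competing risk models**, for patients who leave the ICU alive before day 11: "Assuming no propofol-associated energy intake after ICU discharge alive, we will impute a daily propofol-associated energy intake of 0 for these patients".
- **Data management plan**: "All patient data are pseudonymized and coded with a unique patient identification (ID) number generated by the electronic data management system". It does not say whether this ID links a patient across units or hospital stays.

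**The concern.** The rule that removes duplicates works at unit level, while the primary endpoints belong to the hospital stay and the inference is about patients. Two consequences follow from the text.

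The first concerns precision. Patients readmitted after hospital discharge contribute two or more records by design. A unit effect is shared by all patients of that unit and does not model the extra similarity of two records from one person. If the second record comes from another unit, it absorbs none of it. Standard errors then come out too small.

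The second concerns exposure and is a matter of bias. The selection rule itself foresees patients who return to the same unit during one hospital stay, and discards the return. If it falls within days 0–11, the analysis fills those days with 0 kcal although the patient was in an ICU and may have received propofol. Days 5–11 are the late phase of the primary comparison. The propofol days lost in this way also shorten the lead-time, so later events may not be registered. A stay in a different participating unit is not dropped, but its propofol days sit on another record. The first record still shows zeros, and the second starts its propofol history afresh.

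**Working it through.** **1. The plan's own figure.** Sample size considerations give more than 18,000 patients and a discharge-alive rate of about 70%. 18,000 × 0.70 = 12,600, which agrees with the stated count of more than 10,000 discharges.

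**2. Precision.** The article gives neither the share *s* of records that are second records nor the within-patient correlation *ρ*. Assume *s* = 1–10% and *ρ* = 0.3–1.0. With *N* records of unit variance, of which *sN* are second members of a pair, the variance of the sum is *N* + 2*sNρ*. The inflation relative to independence is 1 + 2*sρ*. Actual coverage of a nominal 95% interval is 2Φ(1.96/√inflation) − 1.

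| *s* | *ρ* | Variance inflation | True SE / stated SE | Coverage |
|---|---|---|---|---|
| 1% | 0.3 | 1.006 | 1.003 | 94.9% |
| 1% | 1.0 | 1.02 | 1.010 | 94.8% |
| 5% | 0.3 | 1.03 | 1.015 | 94.7% |
| 5% | 1.0 | 1.10 | 1.049 | 93.8% |
| 10% | 0.3 | 1.06 | 1.030 | 94.3% |
| 10% | 1.0 | 1.20 | 1.095 | 92.6% |

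This formula is for a mean-type estimate. For an exposure hazard ratio the inflation also depends on how alike the exposure of the two records is. The rows with *ρ* = 1.0 are an upper bound. A patient readmitted after hospital discharge was necessarily discharged alive the first time, so the two records end in distinct events.

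**3. When one event could be registered twice.** Let the first record have *k*₁ propofol days. Let a second record, in another participating unit of the same hospital, start *d* days later with *k*₂ propofol days. Take the lead-time as counted from ICU admission. A shared death or discharge on day *T* of the first clock is registered on both records only if *T* ≤ 2*k*₁ and *T* − *d* ≤ 2*k*₂. A first stay covering days 0–4 holds at most 5 propofol days, so its window is at most 2 × 5 = 10 days, and any later event is not registered on that record.

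**4. Zero imputation and lead-time (hypothetical patient).** The index stay has 3 propofol days, so the window is 2 × 3 = 6 days. The patient returns to the same unit on day 5, receives propofol on 4 days and dies on day 12. Under the plan the return is dropped, its days are coded 0 kcal, and the day-12 death lies outside the 6-day window. With the recorded days the window would be 2 × (3 + 4) = 14 days, and the death would be registered with non-zero late-phase intake.

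**5. One record per patient.** If 10% of records were removed, 18,000 × 0.90 = 16,200 would remain, with 16,200 × 0.70 = 11,340 discharges. At 5% the figures are 17,100 and 11,970; at 1%, 17,820 and 12,474. All exceed the stated 10,000.

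**The case against.** **Rarity.** The survey holds 21,100 adults from 785 units, about 27 per unit (21,100 / 785 = 26.9). With so few patients per unit, entering the same person twice may be rare, and nothing in the article supports a share as high as 5–10%. This stands, and it is why the effect on precision is called probably small.

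**One outcome counted twice.** A reader might infer that any transfer between units makes one hospital death or discharge count as two. The documents do not support that. It would need two participating ICUs in one hospital, the same patient entered by both, more than 48 hours in each, and an event inside both lead-time windows. The article shows none of this. What stands is that the rule as written does not exclude it.

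**The zeros are a declared assumption.** Daily recording stopped at ICU discharge, and the article states openly what it assumes afterwards. That is fair, and the issue is distinct from double counting. But the selection rule acknowledges returns to the unit, for whom the assumption may be false. Neither the listed sensitivity analyses nor the Limitations section addresses them.

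**Detail left to a fuller plan.** Naming a unit random effect does not rule out robust variance elsewhere. This is a reason for moderation. The selection rule and the imputation are nevertheless fixed in the article itself.

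**Feasibility.** Linkage of IDs across units or stays is not confirmed, and a patient-level random effect would be weakly identified when nearly all patients have one record. Both points stand and shape the fix.

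**Conclusion.** The point holds in a limited form. Records of patients readmitted after hospital discharge are explicitly entered as separate cases, and no patient-level clustering is named, so the confidence intervals are somewhat too narrow. Under the assumed ranges, variance is understated by a factor of about 1.006 to 1.20. The upper end requires both a 10% repeat share and full correlation, which does not describe readmission after a live discharge.

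Double registration of one shared hospital event is a gap in the rule, not something the documents show to occur.

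The coding of ICU returns within days 0–11 as zero intake is a separate source of bias, affecting mainly late-phase intake and the lead-time. Its size cannot be given, because the article states no number of such returns. Nothing here threatens the sample size. The issue is worth settling before analysis.

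**What to change.** 1. Analyse the first eligible ICU admission per patient across all participating units, as far as IDs allow linkage. Alternatively, keep later hospital stays, use patient-clustered (robust) variance, and add a sensitivity analysis restricted to each patient's first record. In either case, state how a second stay in another participating unit of the same hospital is handled.
2. Where a second ICU record exists in the same hospital stay within days 0–11, use its recorded propofol and mechanical ventilation days in place of 0, including for the lead-time. Otherwise, exclude or censor such patients in a sensitivity analysis.
3. Report the number of repeat records, and state it as a limitation if linkage is not possible.

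The cost is a sentence or two in the selection rule, a check of the existing IDs and, if needed, one additional model run. Applying the present rule already requires repeat admissions to the same unit to be recognised. The loss of records is affordable on the counts in step 5 of the working.
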